| Objectives | Primary objective: To investigate the of HCQ treatment effects on traditional cardiovascular risk factor profile: blood lipid profile, B-glucose, blood pressure after 4 and 8 weeks in patients with RA and SLE.  Secondary objectives: To study the effect on vascular function, measured with pulse wave velocity (PWV) and inflammatory markers including CRP, cytokines, Calprotectin and Hyaluronan (HA).  To study the patient´s compliance to drug prescription and the occurring adverse events. |
| Study design | A randomized, controlled, open label, multicenter, interventional, phase II study. |
| Study population | Patients with RA (n=24) and SLE (n=24) from the Rheumatology departments in Umeå, Sundsvall, Sunderbyn and Östersund. |
| Duration of treatment | 8 weeks for both groups; for group 1 weeks 1 to 8, for group 2 weeks 5 to 12. After the study, the patients can continue to receive the study medication if their disease condition so requires (determined by the patient´s treating physician, prescription medicine). |
| Eligibility criteria | Inclusion criteria:   - Male or female, 18-65 years of age, who has given written consent for his/her participation to the study¸ Women of Childbearing Capacity (WOCBC) only if willing to comply with effective contraception methods during the course of the trial. Acceptable methods are such as oral contraceptives, contraceptive patches, contraceptive implant, vaginal contraceptive, double-barrier methods (for example, condom and spermicide), intrauterine device (IUD), hormonal IUD - ACR criteria for RA and SLE (4) - < 10mg Prednisolon daily doses - Low-medium disease activity = DAS28 <4.6-RA, SLEDAI-2k <6 SLE (Arthritis accepted)   Exclusion criteria:   - Antimalarial medication less than5 ½-t= *250 days* before study inclusion visit - High disease activity, where cortison adjustment is predictable - Pleuritis or Pericarditis – SLE - Impaired visus and/or colour vision - Auditory nerve damage - Cardiomyopathy - Brach block / atrioventricular block - Hypertension >160/95 - Diabetes - Ongoing medical treatment with digoxin - Re-introduction or recent (within 2 weeks) change in the dosing of NSAIDs, prednisolon, blood pressure lowering medication or antilipide treatment. For disease-modifying agents, within 6 weeks. - Short life expectancy due to other comorbidity - Documented allergy or intolerance to study drug - Severe psychiatric condition or other reason that jeopardize compliance with follow up. - On fertile females, pregnancy assessed by anamnesis and pregnancy test |
| Investigational Medicinal Product (IMP) | Hydroxychloroquine (ATC code P01BA02; Plaquenil ® film-coated tablet 200mg) |
| Dosage and route of administration | Plaquenil ® 200mg p.o. 1 tabl daily, 1+0+0+0 |
| Efficacy evaluation | For efficacy evaluation, subjects will be investigated for the following:   - Total Cholesterol (TC) - Triglycerides (TG) - Low density lipoprotein (LDL) - High density lipoprotein (HDL) - Apolipoproteins - Blood pressure - Pulse wave velocity - Blood-glucose- and HbA1c - Calprotectin in serum - Hyaluronan in serum - CRP - TNFr- 1 och 2, MCP-1, IL-2sR-alfa, IL-6, IL-17 samt IFN-gamma - Compliance to treatment   - Adverse Events  - Compliance to drug prescription |
| Safety evaluation  Safety evaluation | For safety evaluation, the subjects are monitored for compliance including adverse events occurrence. The compliance is measured by controlling drug accountability during patients´site visits. From the time a patient consents to participate in the trial until he/she has completed the trial (without any follow up period), all AEs will be reported in the CRF. All SAEs as defined in the protocol will be reported by filling out and sending the SAE form within 24 hours to *the monitor*. *The sponsor* will determine whether the event qualifies to immediate reporting to the regulatory authorities (SUSAR-reporting) or will be reported in the annual development safety update report (DSUR). SAEs occurring after trial termination must be reported if considered related to the treatment during the trial. |
| Statistical methods | Non-parametric tests will be used. Mann-Whitney´s test; when comparison between groups. Statistical testing of multiple assessments over time; Kruskal-Wallis or Friedmans test and Wilcoxons test. |
| Criteria for evaluation | All subjects enrolled will constitute the analysis population  Primary and secondary endpoints (except safety parameters) will be analyzed according to intention to treat.  Safety parameters will be analyzed as per protocol. |
| Interim analysis | No interim analysis is planned |

- **Background and Rationale**
- **Background**

The two inflammatory diseases Rheumatoid Arthritis (RA) and Systemic Lupus Erythemato-sus (SLE) have the major comorbidity problem of Cardiovascular diseases (CVD) in common. The risk for CVD is overall more than doubled in both RA (1) and SLE compared with population/controls. In SLE, this risk for CVD is emphasized and noted 8 times increased in middle aged women (2, 3). In our further studies of surrogate markers and risk factors for CVD, we could show both an increased Intima-Media thickness and decreased endothelial function in RA compared with controls (4, 5). In SLE we have shown an increased vascular stiffness compared with controls (6). Traditional risk factors (e.g. dyslipidemia and hypertension) for CVD are increased in RA and SLE although with diverging results (7-10).

Klorokin medication is registered as RA treatment and recently shown beneficial in combination with Sulfasalazin and MTX compared with TNF (11). In SLE Klorokin has dual effects in lowering disease activity (especially skin and joint involvement) and preventing flare (12, 13). Retrospective studies of SLE have demonstrated an association between use of Klorokin and improved lipid profile (14), vascular stiffness (15) as well as risk of thrombosis (16). An association between improved blood lipid profile and Klorokin treatment have also been noted in RA (17,18). One interventional noncontroled study showed improvement of cholesterol and low density lipoprotein (LDL) levels in SLE patients on Hydroxychloroquine (HCQ) medication (19). There is also a growing body of evidence that HCQ has a positive influence on glucose metabolism (Hage MP et al 2014).

Hyaluronan (HA), a major component of the extracellular matrix (ECM) has been known as lubricant and shock absorbing in joints. It has also been shown that high molecular size HA (400-2000 kDa) has several regulatory and structural functions (20-22) as well as being anti-inflammatory and immunosuppressive (23,24). Low molecular size HA (10-500 kDa) is in-volved in the induction of NFκB and increase of cyto-and chemokines (25). High molecular size HA can also activate the Toll-like receptors an initiate immune response (20, 26, 27).

The activity of NFκB is known to be decreased in SLE ( 28) leading to a lack of inhibition of apoptosis and promoting chronic inflammatory responses ( 29). The Toll-like receptors play a major role in the pathogenesis of SLE where Hydroxychloroquine (HCQ) has been shown to have an antagonistic effect (30). The surface molecule CD44 participates in T-cell adhesion and migration is increased in SLE patients (28). Among the rheumatic diseases, an epidermal imbalance between HA and its CD44 receptor in patients with Psoriatic Arthritis has recently been demonstrated (31). Both patients with Dermatomyositis and Lupus nephritis have in-creased serum levels of HA (32, 33). However the knowledge of LMW-HA in SLE is scarce, why we find it of great interest to study the serum levels of low disease activity-SLE further-more serum levels of LMW-HA in SLE patients before and after HCQ treatment.

We performed a pilot study as a student project 2013:

Objectives: In earlier, retrospective, studies chloroquine has been found associated with more favorable risk factors; reduced pulse wave velocity (PWV), inflammation, cholesterol and fasting glucose. The purpose of this pilot study was to longitudinally study these effects.

Methods and materials: Nine SLE-patients with low disease activity, median age 54 (44-64), no more than 10 mg prednisone daily and without antimalarials were recruited to our study. Eight patients completed one follow-up, 7 completed the whole study. Two of them had dia-betes treated with insulin. Analysis and measurements were performed before and after 4 and 8 weeks of treatment with 200 mg hydroxychloroquine (HCQ) daily dose. Laboratory tests of inflammation, lipids and glucose were analyzed according to routine. Calprotectin, a novel marker for disease activity, in serum was detected with ELISA in the department of clinical immunology in Umeå. PWV was measured oscillometrical, with the validated device Arterio-graph®.

Results: Beneficial effects on LDL- (3,4±0,9 vs. 3,0±1,0 mmol/l, p=0,016) and HDL-cholesterol (1,6±0,3 vs. 1,8±0,5 mmol/l, p=0,031) were seen after 4 weeks of treatment. After 8 weeks CRP was lowered (5,6±7,4 vs. 2,1±1,8 mg/l, p=0,094), while calprotectin initially increased but after 8 weeks was slightly lower than baseline (523,7±309,8 vs. 716,3±522,4 ng/ml, p=0,023 and 523,7±309,8 vs. 499,5±286,0 ng/ml, p=0,742 respectively). PWV was unchanged, but the youngest patient in the study did show a marked lowering of PWV. We could not show any correlation between PWV, CRP and calprotectin. Among patients without diabetes HbA1c was lowered (37,8±3,3 vs. 35,8±3,8 mmol/mol, p=0,063) while fasting glucose showed no change.

Conclusion: In this pilot study we were able to show, despite few patients, that HCQ affects LDL- and HDL-cholesterol in 4 weeks in SLE-patient, also with low prednisone dosage. Ben-eficial effects on inflammation and glucose levels were also noted. However, no effect on vascular stiffness was shown, which might be related to the relatively high age and substantial amount of comorbidity among the patients.

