Patients with RA (n=24) and SLE (n=24) will be recruited from the Rheumatology depart-ments in Umeå, Sundsvall, Sunderbyn and Östersund. 12 patients with RA and 12 patients with SLE will be randomized to each group. The randomization will be performed by study nurses, not otherwise involved in the conduction of the study, so that patients with RA receive even study numbers (Group 1 or Group 2) and patients with SLE (Group 1 and Group 2) receive uneven study numbers. A randomization list definining each study numbers group identity/treatment regim is prepared in advance by the study team.

- **Eligibility Criteria**
- **Inclusion Criteria**
- Male and female, 18-65 years that have given their written consent to participate in the study; Women of Childbearing Capacity (WOCBC) only if willing to comply with effective contraception methods during the course of trial . Acceptable methods are such as oral contraceptives, contraceptive patches, contraceptive implant, vaginal contraceptive, double-barrier methods (for example, condom and spermicide), intrauterine device (IUD), hormonal IUD.
- ACR criteria for RA and SLE (4)
- < 10mg Prednisolon daily doses
- Low-medium disease activity = DAS28 <4.6-RA, SLEDAI <6 SLE (Arthritis accepted)
- **Exclusion Criteria**

A subject will not be eligible for inclusion in this study if any of the following criteria applies:

- Antimalarial medication less than 5 ½-t i.e. 250 days before inclusion visit
- High disease activity, where cortison adjustment is predictable
- Pleuritis or Pericarditis – SLE
- Impaired visus and/or color vision
- Auditory nerve damage
- Cardiomyopathy
- Brach block / atrioventricular block
- Hypertension >160/95
- Diabetes
- Ongoing medical treatment with digoxin
- Re-introduction or recent (within 2 weeks) change in the dosing of NSAIDs, prednisolon, blood pressure lowering medication or antilipide treatment and within 6 weeks for disease-modifying agents
- Serious comorbidity, including other medications with known drug interactions with medication intended in the present study
- Short life expectancy due to other comorbidity
- Documented allergy or intolerance to the study drug.
- Severe psychiatric condition or other reason that jeopardize compliance with visit schedule
- In case of women of child bearing capacity (WOCBC), pregnancy assessed by anamnesis and pregnancy test
- **Other Eligibility Criteria Considerations**

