To assess any potential impact on subject eligibility with regard to safety, the investigator must refer to the following documents for detailed information regarding warnings, precautions, contraindications, adverse events (AEs) and other significant data pertaining to study drug: Approved national summary of product characteristics (SPC).

- **Treatment within the study**

Hydroxychloroquine (Plaquenil®) 200 mg (Attachment 2. Summary of Product Characteristics) one tablet daily is initiated week 0 for group 1 and at week 5 for group 2and will be continued after the study is closed. All other medication continues during study, but if changes is performed in any medication, that might be a reason for discontinuation in the study (se also Section12.).

- **Withdrawal Criteria and Early Termination**

The subjects have the right to withdraw from the study at any time and for any reason without prejudice to his or her future medical care by the physician or hospital. The investigator also has the right to withdraw subjects from the study in the event of change in eligibility or other reasons.

Discontinuation criteria for individual subjects:

- Withdrawal of consent
- Changes in glucocorticoids, NSAID, ASA as well as medication against hyperlipidemia and hypertension
- Adverse event or serious adverse event related to treatment or investigational procedure that requires discontinuation in the study according to the investigator
- Pregnancy during the study
- **Study Assessments**
- **Demographic and Baseline Assessments**

Demographic information such as gender, age and ethnic origin will be collected in addition to baseline values.

Other baseline assessments are:

- Signed and dated ICF
- Inclusion/exclusion criteria
- Disease history/duration
- Current medication
- Disease activity by index (SLEDAI-2k or DAS 28)
- Vital signs
- WOCBC, pregnancy test
- Visus and color vision
- Blood lipids and-glucos
- See also Schedule of events, Attachment 1.
- **Assessments during the study**

Assessments include blood lipids, vascular stiffness, Calprotectin and Hyaluronan as described in 7.1 and 7.2 and 9.1.
In addition;

- Compliance to treatment
- Adverse events
- Compliance to drug prescription
- **Biobank**

Biobank is available at the Rheumatology Clinic, NUS, Umeå, Sweden (SoS443)

- **Study medication and concomitant medication/therapy**
- **Study medication per treatment group**

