Hydroxychloroquine (Plaquenil®) 200 mg one tablet daily. See also risk-benefit for the individuals (4.2).

- **Administration follow-up of the medication:**

The responsible physicians for the patients will prescribe the study medication to the patients. In case of an adverse event, the study personnel will contact the sponsor. The sponsor will determine whether the event qualifies to immediate reporting to the regulatory authorities (SUSARs) or will be included to the annual development safety update report to Regulatory Authority (SAE). SAEs occurring after trial termination must be reported if considered related to the treatment during the trial.

- **Concomitant Medications**

The prohibited medication are considered at the time of inclusion (see section 10.2.2 “Exclusion Criteria”) and prevent the inclusion of patient not compliant to inclusion/exclusion criteria due to such ongoing medication.

During the study, all concomitant medications taken in both groups studied will be recorded in the patient record according to standard practice. In case a prohibited medication is noticed it results to patient withdrawal from the study (see sections 11. “Treatment within the Study” and 12. “Withdrawal Criteria and Early Termination”).

- **Adverse Event and Serious Adverse Event Collection, Recording and Reporting**

Known complications of RA and SLE will not be considered as a AE/SAE.

The investigator is responsible for detection and documentation of events meeting the criteria and definition of an adverse event (AE) or serious adverse event (SAE), as provided in this protocol. During the trial when there is a safety evaluation, the investigator or site staff will be responsible for reporting AEs and SAEs, as detailed in this section of the protocol. Clinically significant AEs considered by the investigator to be related to treatment will be followed until resolved or considered stable. It will be left to the investigator’s clinical judgment to determine whether an AE is related and of sufficient severity to require the subject’s removal from treatment or from the trial. A subject may also voluntarily withdraw from treatment due to what he or she perceives as an intolerable AE. If either of these situations arises, the subject should be strongly encouraged to undergo an end of trial assessment and be under medical supervision until symptoms cease or the condition becomes stable.

- **Definition of Adverse Events and Serious Adverse Events**

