**Recovered/resolved**

**Recovering/resolving**

**Not recovered/not resolved**

**Recovered/resolved with sequelae**

**Fatal**

**Unknown**

- **Time Period, and Frequency of Detecting AEs and SAEs/SUSARs**

From the time a patient consents to participate in the trial until he/she has completed the trial (without any follow up period), all AEs will be reported in the CRF. All SAEs will be reported promptly to *the sponsor*. SAEs will be reported by filling out and sending the SAE form within 24 hours to *the monitor* once the investigator determines that the event meets the protocol definition of an SAE. *The sponsor* will determine whether to whether the immediate notification to the regulatory authorities is required. SAEs occurring after trial termination must be reported if considered related to the treatment during the trial.

After the initial SAE report the investigator is required, proactively, to provide further information regarding the patient’s condition. All follow-up information must be forwarded to *the sponsor and monitor* as it becomes available. The investigator must follow-up all patients with SAEs until the event has subsided (or disappeared), the condition has stabilized, the event is otherwise explained or the patient is lost to follow-up.

For all deaths reported at any time, available autopsy reports and relevant medical reports should be forwarded to *the sponsor*.

Information about a suspected unexpected serious adverse reaction (SUSAR) which occurs during the course of the trial and is fatal or life-threatening will be reported *by the sponsor* as soon as possible to the regulatory authority (directly, and via them to EudraVigilance Clinical Trials Module) and the relevant ethics committee.

This will be done no later than 7 days after *the investigator* first became aware of the reaction. Any additional relevant information should be sent within 8 days of the initial report. A SUSAR, which is not fatal or life threatening will be reported by *the sponsor* as soon as possible, and no later than 15 days after becoming aware of the reaction to the competent authorities (directly, and via them to EudraVigilance Clinical Trials Module) and the relevant ethics committee.

- **Pregnancies and Breast Feeding**

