Subjects who become pregnant during the trial must be withdrawn. The subject will be asked to attend follow-up visits and the outcome of the pregnancy will be followed including reporting on the state of the child 8 to 12 weeks after delivery. Patients receiving treatment shall not breast feed their children.

- **Data Analysis and Statistical Considerations**
- **Sample Size Considerations**

Twenty patients in each group are needed for a 80%-ig power of lowering blood-pressure 10 mmHg. Lowering LDL or TC 0.65 mmol/L with SD 0.7 gives a power of 0.816 when 20 pati-ents in each group are included.

- **Data Sets and Populations**

All subjects enrolled will constitute the analysis population.

- **Interim Analysis**

No interim analysis will be performed

- **Key Elements of Analysis Plan**

Non-parametric tests will be used. Mann-Whitney´s test; when comparison between groups. Statistical testing of multiple assessments over time; Kruskal-Wallis or Friedmans test and Wilcoxons test.

- **Study Administration**
- **Procedure for obtaining informed consent**

Eligible individuals in the study will be contacted by mail containing information about the study, informed consent and return envelope.

- **Definition of Source Data**

All completed assessment scales will be collected in patient specific binders and regarded as source data. All patient related activities of medical relevance will also be documented in the patient hospital record

- **Quality Control**

The trial will be monitored consistent with the demands of the trial and site activity to verify that the:

- Safety and rights of subjects are being protected
- Data are authentic, accurate, and complete
- Trial is conducted in accordance with the currently approved protocol and any other trial agreements, GCP and all applicable regulatory requirements. The investigator and the head of the medical institution (where applicable) agrees to allow *the monitor* direct access to all relevant documents.

An external monitor for the study, not involved in any aspect of the treatment of the individuals participating in the study, will be appointed. The monitor will be appropriately trained, and has the scientific and/or clinical knowledge needed to monitor the trial adequately.

The monitoring will take place in accordance to GCP before, during and after the trial. If any misconduct or neglect would be notified the sponsor and investigator will be notified for to corrective and preventive actions.

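### The synopsis takes safety out of intention to treat and assigns it to an undefined per-protocol analysis, which conflicts with the all-enrolled population and would tend to understate adverse events

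*Protocol*

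**What the plan says.** Section 4 (Synopsis), row Criteria for evaluation, makes three statements in sequence. First, "All subjects enrolled will constitute the analysis population". Second, "Primary and secondary endpoints (except safety parameters) will be analyzed according to intention to treat". Third, "Safety parameters will be analyzed as per protocol". Section 16.1.1 repeats the first statement and mentions neither the exception nor a per-protocol set. No section defines a per-protocol or a safety population.

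Section 12 lists the reasons for discontinuing a patient. They include "Adverse event or serious adverse event related to treatment or investigational procedure that requires discontinuation in the study according to the investigator", "Changes in glucocorticoids, NSAID, ASA as well as medication against hyperlipidemia and hypertension", and pregnancy. The introduction to section 15 adds that "A subject may also voluntarily withdraw from treatment due to what he or she perceives as an intolerable AE". On collection, section 15.3 states that from consent "until he/she has completed the trial (without any follow up period), all AEs will be reported in the CRF".

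Adverse events and compliance are secondary endpoints in section 7.2. Section 10.1 fixes the numbers: "12 patients with RA and 12 patients with SLE will be randomized to each group".

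**The concern.** Per-protocol analysis normally keeps patients who took the treatment and completed follow-up as planned. For safety this selects on the outcome, because a patient who cannot tolerate the drug is likely to stop and so leave the set. What remains describes tolerability among those who tolerated the drug, and the error is in the reassuring direction.

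This is not a detail left to a later analysis plan. The protocol itself names a set for safety, and an analysis plan that used all treated patients would have to depart from it. Adverse events are a stated endpoint, and with 48 patients a few exclusions can visibly change the result.

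**Working it through.** **The protocol's own figures.** It gives no figure on this point. Its one reproducible calculation is the power of 0.816 for a 0.65 mmol/L difference with SD 0.7 and 20 per group. A two-sample t-test at two-sided 5% (an assumption, since alpha is not stated) gives 0.8163. That figure is sound and does not depend on the safety set.

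**What the wording can mean.**
- The synopsis row gives intention to treat to every endpoint except safety, then gives safety its own rule. In that contrast, per protocol names a population.
- The alternative reading, that safety is analysed as this protocol describes, leaves the exception without purpose, because section 16 describes no separate safety analysis.
- On the first reading the rule contradicts the all-enrolled statement in the same row and in 16.1.1. On the second, the exception has no content and the row still needs rewording.

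**Inputs for the size.** Patients randomised: 2 groups × (12 + 12) = 48 (section 10.1). Assumed: all 48 take at least one dose; d patients stop because of an adverse event; a other patients have an event and do not stop. The protocol gives no value for d or a.

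**Formulas.** All patients: (a + d)/48. Per protocol, leaving out the d stoppers: a/(48 − d). The difference is d(48 − a − d) / [48(48 − d)], which is positive whenever d > 0 and at least one patient has no event.

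| d | a | All patients | Per protocol | Difference |
|---|---|---|---|---|
| 2 | 5 | 7/48 = 14.6% | 5/46 = 10.9% | 3.7 points |
| 3 | 5 | 8/48 = 16.7% | 5/45 = 11.1% | 5.6 points |
| 5 | 10 | 15/48 = 31.3% | 10/43 = 23.3% | 8.0 points |

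Check of the second row: 3 × 40 / (48 × 45) = 120/2160 = 5.6 points.

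**Events leading to discontinuation.** Per protocol these are 0% whatever d is. In all patients they are 4.2% (d = 2), 6.3% (d = 3) or 10.4% (d = 5).

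**Chance that the rule matters.** The probability of at least one such stopper among 48 is 1 − (1 − q)^48. For an assumed risk q of 2%, 5% or 10% this is 62%, 91% or 99%.

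**The case against.** The strongest reply is that the protocol never says stoppers are left out. Section 12 governs leaving the study, not leaving an analysis set. A patient who stops for an adverse event has followed the protocol rather than deviated from it. The row also opens with all enrolled subjects. This stands in part: the removal of stoppers follows from ordinary usage together with section 12, and is not written down. It does not rescue the sentence, because the contradiction remains whichever reading is taken.

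It is also fair to say that no safety data are lost. All adverse events are recorded from consent, withdrawal for an adverse event has its own forms, and expedited reporting is independent of any analysis set. An all-patient table therefore remains possible. But collection does not settle which patients are analysed.

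A reader might infer several stronger things that the documents do not support:
- With 3 stoppers, that the adverse-event rate falls from 3/48 = 6.3% (exact 95% CI 1.3 to 17.2%) to 0/45 (0 to 7.9%). That contrast holds only for events leading to discontinuation, or if no other patient has any event.
- That the pilot shows how many will stop for adverse events. It reports 7 of 9 completing and gives no reasons, so its 2 non-completers support no particular rate.
- That compliance will certainly be overstated. Compliance appears under both the efficacy and the safety evaluation in the synopsis, so whether the rule reaches it is unclear. If it does, measuring compliance among compliers would be circular.

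**Conclusion.** The point holds as a contradiction with a likely direction of bias. The synopsis assigns safety to a per-protocol analysis that is defined nowhere and that conflicts with the all-enrolled population in the same row and in 16.1.1. If the term has its usual meaning, adverse-event proportions are biased downwards and events leading to discontinuation vanish from the results.

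Under the assumed counts the understatement is about 4 to 8 percentage points. These are illustrations resting on assumed values of d and a, on all 48 being dosed, and on the removal of adverse-event stoppers only. The intention-to-treat analysis of the lipid endpoint and the stated power are untouched.

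**What to change.** Delete the per-protocol sentence and the exception for safety in the synopsis, and use the same wording there and in 16.1.1, for example:

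*Safety is analysed in all randomised patients regardless of discontinuation. Adverse events are counted from enrolment and tabulated by exposure period: untreated, or on HCQ from first dose. On-treatment rates use all patients who took at least one dose. The comparison of Group 1 (on HCQ) with Group 2 (untreated) over weeks 0 to 4 uses all randomised patients, including Group 2 patients who withdraw before starting. Compliance is analysed in all patients who were prescribed the study drug.*

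Limiting the whole safety analysis to dosed patients from first dose would not be enough. It would discard Group 2's untreated weeks, which are the only concurrent control, and lose Group 2 patients who leave before dosing.

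The cost is a short text change in two places. No new data are needed: events are recorded from consent, and Attachment 1 already schedules an adverse-event assessment at week 4.
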